### Treatment

2.5

Participants will receive EMDR therapy in accordance with standardized clinical protocol (Hofmann et al., 2015; Shapiro, 2018). In line with the real-world nature of this study, the number of EMDR sessions will not be *a priori* defined. However, after each session, therapists will specify the session type (EMDR or non-EMDR) in REDCap. Therapists will exercise clinical judgment in selecting session type, and the exact session date, type, and key contextual variables (e.g., symptom severity, medication changes, major life events) will be recorded to permit adjustment for time-varying confounding in the analysis.

### Sample size estimation

2.6

There is no established method for estimating sample size on N-of-1 trial designs in observational settings. Following Senn’s (2019) recommendations, and the practical guidance of Yang et al. (2021), at least 32 therapist-patient dyads, with a minimum of 26 visits per participants, approximately 1 visit/week for 6 months. Yang et al. suggests that roughly 24 repeated measurements per individual provide reasonable power to detect a moderate within-patient effect (Cohen’s d around 0.5), when aggregating results across multiple N-of-1 series. We expect a small number of patients to record fewer than 24 outcome measurements. However, since follow-up can extend up to 18 months, some patients will likely record considerably more measurements. Moreover, because the Bayesian hierarchical model naturally down-weights individual patients with less precise within-patient estimates, participants with fewer observations will contribute less to the pooled effect. As a result, a small number of shorter series should not materially reduce the precision of the overall estimate.

### Statistical analysis

2.7

We will begin with a descriptive analysis of demographic, clinical, and outcome variables. Quantitative variables will be summarized using the mean and standard deviation if the assumption of normality is met; otherwise, the median and interquartile range will be reported. Qualitative variables will be described using absolute counts and percentages.

Differences between personality and personal beliefs groups will be evaluated using appropriate statistical tests: Student’s t-test for normally distributed quantitative variables, Mann–Whitney U test for non-normally distributed quantitative variables, and either the Chi-square test or Fisher’s exact test for categorical variables, as appropriate.

Sessions with missing values on treatment (i.e., EMDR or no-EMDR session) or outcome (i.e., PHQ-9 final score) will be excluded from the following analyses.

To assess the impact of psychological functioning at baseline on the base of personality domains and pathogenic personal beliefs on EMDR’s effect on depressive symptoms, we will combine data from multiple N-of-1 trials using a Bayesian multilevel time-series model (Schmid and Yang, 2022).

Session-level outcomes (PHQ-9 scores) are nested within patients. The model will include patient-specific random intercepts and random slopes for the EMDR effect. To model temporal dependence, residuals at the session level will incorporate an AR(1) structure, capturing correlation between consecutive measurements within each patient. Weakly informative priors will be used for all regression coefficients (Normal[0,5]) and for the standard deviations of random effects (half-Normal[0,2]), while the AR(1) correlation parameter will have a uniform prior on (−1,1). Missing session-level outcomes will be handled directly within the hierarchical framework under a missing-at-random assumption, allowing all available repeated measurements to contribute to estimation. Patients with fewer sessions will be naturally down-weighted via partial pooling, without the need for imputation. Sensitivity analyses will explore alternative residual correlation structures (e.g., ARMA[1,1]), inclusion/exclusion of patients with very few sessions, and adjustment for time-varying covariates to assess potential confounding. Model convergence will be assessed through trace plots, $\hat{R}$statistics ($\hat{R}$≤1.01), and effective sample size for all parameters. Posterior predictive checks will be used to evaluate model fit and the adequacy of assumptions.

We will also perform secondary analyses using anxiety symptoms as outcome, and will evaluate the effect of other predictors and moderators (e.g., dissociation, post-traumatic symptoms, emotional dysregulation, and sleep difficulties). Missing sessions will be handled directly in the longitudinal model. Because the primary analysis uses a Bayesian hierarchical time-series model, missing outcome data are accommodated under a missing-at-random (MAR) assumption without requiring imputation or exclusion of the entire individual. Dropout will be recorded by therapists together with the stated reason, and dropout patterns will be summarized descriptively.

All analyses will be conducted using R version 4.5.0 (R Core Team, 2025).

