**Objective:**

This study aims to present a protocol for evaluating factors associated with EMDR therapy effectiveness for depressive symptoms in real-world clinical settings. The primary objective is to identify individual characteristics that may predict treatment response. Secondly, we aim to examine potential moderating factors of EMDR for depressive symptoms, including psychologically associated symptoms and therapeutic relationship.

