#### Primary objectives

1.1.1

The primary objective of this study is to identify potential predictors of EMDR therapy outcomes in individuals with depressive symptoms in real-world clinical settings. More specifically, we hypothesized that a lower individual psychological functioning at baseline, with a high dysfunctional personality domains and pathogenic personal beliefs, influence the effect of EMDR in treating depressive symptoms. Moreover, we aim to assess whether changes in individual psychological functioning during therapy modify therapy outcomes.

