#### Secondary objectives

1.1.2

The secondary objective is to examine other potential moderators of the EMDR for depressive symptoms. We hypothesized that psychological associated symptoms (anxiety, dissociation, post-traumatic symptoms, emotional dysregulation, and sleep difficulties) at baseline are related to a smaller reduction in depressive symptoms. Furthermore, since the therapeutic relationship is described as a core element of EMDR therapy, we intend to evaluate the role of working alliance in treatment progress and outcomes.

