Through the integration of innovative methodologies using N-of-1 trials, meta-analysis and meta-regression, this study contributes to deepening our understanding of factors influencing the effectiveness of EMDR and its application in natural settings. Additionally, the design of our study offers the opportunity to explore both patient and therapist characteristics and process variables in real-world clinical settings, with a broad range of measures assessed on multiple occasions. Indeed, as Kazdin (2007) suggested, assessment on a session-by-session basis (i.e., every time before and after each session over the course of treatment) is useful for evaluating the mediator of change and symptom reduction and considering individual differences during these changes.

For our first objective, we expect that profiling individual psychological functioning at baseline will be associated with the severity of depressive symptoms at baseline and during EMDR therapy. Although several studies have examined the relationship between personality and mental health treatment (Bucher et al., 2019), the literature has shown a limitation in assessing personality dimensions only at the beginning of therapy (Samuel et al., 2018). For these reasons, we expect that collecting personality and pathogenic belief ratings at the end of therapy will have the potential advantage of capturing more data for therapists and allowing clearer prediction of longer-term treatment outcomes in clinical reality.

Moreover, the structure of our study supports real-world evidence through the longitudinal evaluation of other potential factors that potentially play an important role in adapting effectiveness of EMDR treatment. Indeed, these findings could inform a more nuanced understanding of the mediating role of individual and process factors of EMDR therapy in associations with depressive symptoms severity.

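### The primary model estimates moderators of an EMDR versus no-EMDR session contrast, while the objectives also concern response over the course of therapy

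*Protocol article*

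**What the plan says.** The Abstract states the aim as: "The primary objective is to identify individual characteristics that may predict treatment response". Section 1.1.1 words it as: "The primary objective of this study is to identify potential predictors of EMDR therapy outcomes in individuals with depressive symptoms in real-world clinical settings". It adds that "we aim to assess whether changes in individual psychological functioning during therapy modify therapy outcomes". Section 1.1.2 hypothesises that associated symptoms "at baseline are related to a smaller reduction in depressive symptoms". All four are most naturally read as statements about a course of therapy.

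Section 2.7 works at another level. Its exclusion rule shows what counts as treatment and as outcome: "Sessions with missing values on treatment (i.e., EMDR or no-EMDR session) or outcome (i.e., PHQ-9 final score) will be excluded from the following analyses". The purpose of the model is given as: "To assess the impact of psychological functioning at baseline on the base of personality domains and pathogenic personal beliefs on EMDR’s effect on depressive symptoms". Its structure is: "The model will include patient-specific random intercepts and random slopes for the EMDR effect", with AR(1) residuals. The section names no term for time or stage of therapy. Adjustment for time-varying covariates appears as a sensitivity analysis. Under section 2.5 the therapist decides the type of each session.

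Table 1 schedules PHQ-9 at T0a, T0b, before sessions, and at T6, T12 and T-END. BDI-II is scheduled at T0a, T6, T12 and T-END.

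**The concern.** The session contrast compares a patient's PHQ-9 at EMDR sessions with the same patient's PHQ-9 at other sessions. Response over the course is how far PHQ-9 falls from start to finish. A patient who recovers and a patient who never changes can have the same session contrast, and a patient who has only EMDR sessions after T0b has none.

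Two errors of interpretation could follow. A characteristic that separates those who improve from those who do not may show no interaction with session type, and the null may then be reported as failure to predict response. Conversely, if the share of EMDR sessions rises during therapy and the model has no time term, part of the decline is credited to session type. A predictor of decline can then look like a moderator of the EMDR effect.

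**Working it through.** **1. The plan's own figures (section 2.6).** The plan gives 32 dyads and at least 26 visits, about weekly for 6 months. 365.25/2/7 = 26.1 weeks, so the visit count agrees. Power cannot be reproduced, because alpha, target power and between-patient SD are not given. Assume two-sided alpha 0.05, 24 measurements split equally, independent residuals and d = 0.5:

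- One series (12 v 12): power 23%.
- 32 pooled series: SE = sqrt((tau² + 4/24)/32), power = Φ(0.5/SE − 1.96). This exceeds 99% for tau from 0 to 0.5 and is 74% for tau = 1.0 (in d units).

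This justification concerns the average session contrast, not predictors of response.

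**2. Size of the gap for one patient.** Inputs: 26 visits less the four sessions before T0b leaves 22. Assumed: PHQ-9 falls linearly from 20 to 8.

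- Step per session: 12/21 = 0.57.
- Alternating types: the two session means differ by one step, 0.57 points.
- 13 EMDR and 9 other sessions in random order: mean contrast 0. The SD of the 22 scores is 3.71, so the SD of the contrast is 3.71 × sqrt(1/13 + 1/9) = 1.61.
- A patient who does not change: 0 in both cases.

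A 12-point difference in response between two patients thus appears as about half a point, or as noise around zero.

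**3. Illustrative simulation across patients.** 32 patients × 26 sessions, residual SD 3 with AR(1) 0.5, mean decline 6 points, mean session effect −1 point, 600 runs per scenario. Each patient's contrast was estimated by least squares and then regressed on the predictor. Course change was the mean of the last three scores minus the mean of the first three.

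| Predictor acts on | Session types | Session-contrast interaction: mean, % significant | Course-change slope: mean, % significant |
|---|---|---|---|
| Decline only (2 points per SD) | 50% EMDR throughout | −0.01, 4.5% | 1.82, 70% |
| Decline only | EMDR later, no time term | 0.46, 31% | 1.83, 70% |
| Decline only | EMDR later, time term | 0.04, 3.7% | 1.85, 70% |
| Session contrast only (1 point per SD) | 50% EMDR throughout | 1.01, 92% | −0.01, 5.5% |
| Session contrast only | EMDR later, time term | 1.00, 96% | 0.55, 13.5% |

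With a constant mix of session types, each analysis sees its own quantity and misses the other at chance level. With EMDR sessions later, the time term removes the false interaction.

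**4. Change in functioning.** Table 1 measures PID-5-BF at T0a and T-END only, and PBS-R at T0b and T-END only. Change in either is known only when therapy ends, so relating it to therapy outcome needs a course-level quantity.

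**5. Precision of a course-level analysis.** With one outcome per patient, n = 32 and two-sided alpha 0.05 (assumed), the correlation detectable with 80% power is tanh((1.96 + 0.84)/sqrt(29)) = 0.48. Power is 19%, 38%, 63% and 84% for r = 0.2, 0.3, 0.4 and 0.5.

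**The case against.** The session contrast can be defended as a deliberate definition of response. The hypothesis in section 1.1.1 speaks of influence on the effect of EMDR, which matches the purpose stated in 2.7. The Introduction ties variability in response to designs in which patients are their own controls. Course-level change has no comparison and mixes any EMDR effect with natural course, regression to the mean and medication. The one-patient example also builds in a fall unrelated to session type, so it shows that the two quantities differ, not that the planned one is wrong. All of this stands. It is why the session model should stay and why a course-level result cannot be called an EMDR effect.

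It does not remove the mismatch. A smaller reduction in depressive symptoms (1.1.2) is hard to read as a contrast between session types, and neither the Abstract nor 1.1.1 says that response is meant in that sense.

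A reader might go further and infer that predictors are never tested, or that the session contrast in PHQ-9 is the only planned outcome analysis. The article does not support this. Section 2.7 states moderation by baseline functioning as the model's purpose and adds anxiety as an outcome with other predictors and moderators, and the Abstract plans a meta-regression. Nor does the absence of BDI-II from 2.7 show that it will go unused, since an article condenses its analysis plan. The Discussion says "we expect that profiling individual psychological functioning at baseline will be associated with the severity of depressive symptoms at baseline and during EMDR therapy". Higher PHQ-9 throughout, without any difference in response, would fit that expectation, but it is an expectation and not a criterion for success.

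**Conclusion.** The mismatch is real and bears on the primary objective and the secondary hypothesis. Predictors are tested, but as moderators of a session-type contrast, and that quantity does not stand in for improvement over therapy. In the illustrations, a 12-point fall leaves a contrast of 0.57 points or of 0 on average. A predictor of decline alone is flagged at chance level (4.5%) when the mix of session types is constant, and falsely in 31% of runs when EMDR sessions come later without a time term.

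These sizes rest on assumed trajectories, session mixes and variances, and on a two-stage least-squares analysis rather than the planned Bayesian model. Its AR(1) residuals could absorb part of a trend, so 31% shows the direction of the risk and does not forecast the planned analysis. That the two quantities differ does not depend on these values.

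**What to change.** In section 2.7:

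- Keep the session-type model as the session-level question, judge it on the predictor-by-EMDR term, and add time since T0b.
- Add a course-level analysis, labelled exploratory: PHQ-9 at T6, or the predictor-by-time term in the session-level PHQ-9 series. Adjust for PHQ-9 at the time the predictor was measured: T0a for PID-5-BF, GAD-7 and MSQ; T0b for PBS-R, DES-II, PCL-5 and DERS. Table 1 first collects the latter group after four sessions, so adjusting only for T0a would let early improvement leak into the predictor.
- Use BDI-II change from T0a to T6 as a supporting measure for T0a predictors only, because BDI-II is not collected at T0b.
- Report the course-level result as prediction of outcome under EMDR therapy, not of an EMDR effect. Do not report a null session-contrast interaction as failure to predict response.

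If the course-level analysis is not added, reword the objectives to the session-level question.

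The cost is wording, one model term and one further regression on scheduled data. The downside is imprecision: 32 patients give 80% power only for r of about 0.48. T6 is a common time point but not always the end of therapy, which may run to 18 months. Data collection is ongoing and completion is expected in December 2027, so this can be settled before analysis.

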### Measurements

2.4

The Beck Depression Inventory (BDI-II, Beck and Steer, 1993) is a 21-item self-report instrument used to assess the severity of depressive symptoms based on DSM-IV criteria. The total score ranges from 0 to 63, with higher scores indicating greater levels of depression. A score above 13 is considered the cut-off for depressive symptoms (14–19: mild depression; 20–28: moderate depression; ≥29: severe depression).

The Patient Health Questionnaire-9 (PHQ-9, Kroenke et al., 2001) is a 9-item self-report questionnaire to measure depressive symptoms in the past 2 weeks based on DSM-IV and DSM-5 major depressive disorder. Participants rate the frequency of symptoms on a scale from 0 (“not at all”) to 3 (“nearly every day”), with total scores indicating no symptoms (0–4 points), mild symptoms (5–9 points), moderate symptoms (10–14 points), moderately severe (15–19 points), severe symptoms (≥20 points). A score ≥ 10 is typically considered indicative of clinically significant depressive symptoms. The Personality Inventory for DSM-5 – Brief Form (PID-5-BF, Krueger et al., 2013) is a 25-item self-report measure to assess five personality domains: negative affect, detachment, antagonism, disinhibition, and psychoticism. Each domain consists of 5 items rated on a 4-point scale ranging from 0 (“very false or often false”) to 3 (“very true or often true”). The total score ranges from 0 to 75, with higher scores indicating greater personality dysfunction, while individual domain scores range from 0 to 15. Consistently high scores in a particular domain may indicate significant and challenging areas for the patient that may warrant further assessment, treatment, or follow-up.

The Pathogenic Beliefs Scale-Revised (PBS-R, McCollum et al., 2024) is a 21-item self-report measure to evaluate the presence of a maladaptive personal beliefs and the distress associated with them on a 4-point Likert scale, ranging from 0 (“not at all”) to 3 (“highly”). The PBS-scale provides four scores: total score, undeserving, cannot rely on others, and guilt.

The Generalized Anxiety Disorder-7 (GAD-7, Spitzer et al., 2006) is a 7-item self-report instrument designed to measure the frequency of generalized anxiety symptoms over the previous 2 weeks on a scale from 0 (“not at all”) to 3 (“nearly every day”). Total scores indicate no symptoms (0–5 points), mild symptoms (6–10 points), moderate symptoms (11–15 points), or severe symptoms (greater than 15 points).

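### On the raw PHQ-9 scale, half-Normal(0,2) is an informative prior for the random-intercept SD, not the weakly informative one the protocol describes

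*Protocol article*

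**What the plan says.** Section 2.7 fixes the priors in one sentence: "Weakly informative priors will be used for all regression coefficients (Normal[0,5]) and for the standard deviations of random effects (half-Normal[0,2". One prior thus serves every coefficient, and one serves every random-effect standard deviation. There are two such standard deviations: "The model will include patient-specific random intercepts and random slopes for the EMDR effect". The outcome is unscaled as written: "Session-level outcomes (PHQ-9 scores) are nested within patients".

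Section 2.4 says the PHQ-9 "is a 9-item self-report questionnaire to measure depressive symptoms in the past 2 weeks", with items scored 0 to 3. The total therefore runs 0 to 27, with severity bands about 5 points wide up to "moderately severe (15–19 points), severe symptoms (≥20 points"). For the PID-5-BF, "The total score ranges from 0 to 75, with higher scores indicating greater personality dysfunction"; its domains run 0 to 15, and the DES-II runs 0 to 100.

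Section 2.2.2 admits patients with clinically significant symptoms in any one of four domains, so depression itself is not required. The sensitivity analyses in section 2.7 vary the residual correlation, the inclusion of patients with few sessions, and time-varying covariates. None varies the priors. Posterior predictive checks are planned.

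**The concern.** A weakly informative prior should leave plausible values of a parameter comfortably inside its mass. Because entry does not depend on depression, patients' usual PHQ-9 levels may run from none to severe. A spread from 4 to 20 as plus or minus 2 SD already needs an SD of 4, and half-Normal(0,2) has only 4.6% of its mass beyond that.

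If the intercept SD is pulled down, the model understates how much patients differ for reasons it does not explain. Intervals for associations between a baseline trait and a patient's depression level then become too narrow. The Discussion expects such an association under the first objective, at baseline and during therapy.

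A second, smaller problem is that one Normal(0,5) serves coefficients whose units differ several-fold, so the same prior means different things for different predictors.

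**Working it through.** The priors carry no derived figure to reproduce. The design inputs are 32 patients and 26 visits each (section 2.6).

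**Assumptions, not in the documents:** between-patient SD τ from 3 to 7 points; within-patient residual SD 3; AR(1) correlation 0.5. The second argument of each prior is read as an SD.

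**1. The prior alone.** For half-Normal with scale 2, P(SD > k) = 2[1 − Φ(k/2)].

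- k = 3: 13.4%
- k = 4: 4.6%
- k = 5: 2[1 − Φ(2.5)] = 1.2%
- k = 6: 0.27%

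The median is 1.35 and the 95% point is 1.96 × 2 = 3.92. At the median, 95% of patients would lie within ±1.96 × 1.35 = ±2.6 points, about one severity band. If the 2 were a variance (scale 1.41), P(SD > 5) would be 0.04%.

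**2. After the data.** The sampling variance of a patient's mean over 26 AR(1) visits is v = 9 × [26 × 3 − 4]/26² = 9 × 74/676 = 0.99. Regressing 32 patient means on one standardised baseline predictor leaves a residual sum of squares S on 30 degrees of freedom. The posterior for τ is proportional to (τ² + v)^(−15) × exp{−S/[2(τ² + v)]} × prior(τ). The slope interval averages Normal(b, (τ² + v)/Sxx) over that posterior. With 4,000 simulated trials per cell, the Monte Carlo error on coverage is about 0.4 points.

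| True τ | Posterior mean SD, half-N(0,2) | Shortfall | Slope coverage, half-N(0,2) | Posterior mean SD, half-N(0,5) | Slope coverage, half-N(0,5) |
|---|---|---|---|---|---|
| 3 | 2.95 | 1.7% | 94.6% | 3.07 | 94.8% |
| 4 | 3.83 | 4.3% | 93.5% | 4.07 | 94.6% |
| 5 | 4.66 | 6.8% | 93.0% | 5.07 | 95.6% |
| 6 | 5.41 | 9.8% | 92.1% | 6.04 | 94.0% |
| 7 | 6.14 | 12.3% | 92.5% | 6.96 | 94.2% |

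The shortfall is (true − posterior mean)/true; for τ = 6 it is (6 − 5.41)/6 = 9.8%. Across this and separate calculations, slope coverage at τ = 5 to 7 falls between about 91% and 94%.

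**3. The EMDR-slope SD.** For true values of 1, 2 and 3 points, the posterior median under half-Normal(0,2) is 0.97, 2.00 and 2.94. Under a flat prior it is 1.00, 2.06 and 3.09. The prior suits this parameter.

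**4. Normal(0,5) and units.** The prior's 95% range is ±1.96 × 5 = ±9.8 PHQ-9 points per unit of predictor. That is per point on a 0–15, 0–75 or 0–100 scale if predictors are raw, and per SD if they are standardised.

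**5. Uncentred intercept.** If the intercept counts among the regression coefficients, a mean PHQ-9 of 10 to 15 lies 2 to 3 prior SDs from zero. With τ = 5, SE² = (25 + 0.99)/32 = 0.81. The data keep weight 25/(25 + 0.81) = 0.969, so the pull is 0.031 × 10 to 0.031 × 15, about 0.3 to 0.5 points.

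**The case against.** The strongest reply is that the primary hypothesis (section 1.1.1) and the model description ask how baseline functioning alters the effect of EMDR. The random-slope SD governs that question, and half-Normal(0,2) is adequate there. This stands, and it limits the point to associations with depression level.

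Second, the SD of 5 to 7 is assumed. The model's intercept SD is also what remains after baseline predictors. If they explain 20 to 40% of the variance (assumption), an SD of 5.5 becomes 5.5 × √0.8 = 4.9 to 5.5 × √0.6 = 4.3, where the loss is smaller. This also stands.

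Third, scaling and centring are often left to an analysis plan or code, and if the outcome were standardised the objection to half-Normal(0,2) would disappear. That is fair as regards the silence. But the article itself prints the prior values, names PHQ-9 scores as the outcome and applies the label, so the label can be judged on the scale given.

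A reader might infer three stronger things that the documents do not support:

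- **That the prior practically forbids a realistic spread.** It makes one unlikely beforehand, but 32 patients largely override it.
- **That Normal(0,5) is wrong because it hardly shrinks.** Little shrinkage is consistent with being weakly informative, and the plan never offers this prior as protection against many predictors.
- **That a family-wise false-positive rate can be computed over the PID-5-BF and PBS-R scores.** The PBS-R total overlaps its own subscores. The plan does not say that all the scores enter one model, and it sets no rule based on intervals excluding zero.

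**Conclusion.** The point holds in a limited form. On the PHQ-9 scale as written, half-Normal(0,2) is informative for the random-intercept SD. If that SD is 5 to 7 points, it is underestimated by about 7 to 12%, and nominal 95% intervals for between-patient associations with depression level lose roughly 1 to 4 points of coverage. At an SD of 3 nothing material happens. The primary moderation question is little affected.

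The sizes rest on the assumed between-patient SD, on a residual SD of 3 with correlation 0.5, and on PHQ-9 being analysed unstandardised. The mixed units under Normal(0,5) and the uncentred intercept are matters of clear specification; the intercept pull is under half a point.

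**What to change.** - Give the random-intercept SD its own, wider prior on the PHQ-9 scale, for example half-Normal(0,5). Keep half-Normal(0,2) for the EMDR-slope SD.
- State that PHQ-9 is analysed in raw points and that the second argument of each prior is an SD.
- Standardise continuous predictors so that Normal(0,5) means the same for each, and centre the intercept.
- Add one run with the priors as now printed to the sensitivity analyses.

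The choice of primary predictors need not change: the personality domains named in the hypothesis can stay as they are.

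The cost is a few lines of text, one more model run and slightly wider intervals for between-patient associations. Data collection is under way with completion expected in December 2027, so the change can be recorded before the analysis.
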